### Data Collection Procedure and Instruments

The baseline data will be collected using a tool with 2 sections: demographic and clinical parameters. Adherence to lifestyle practices will be assessed using the adherence scale on lifestyle practices developed by the researchers, with a maximum score of 12. Adherence will be categorized as “adherent” for those achieving ≥80% (a score of ≥10) and “nonadherent” for those scoring <80% (a score of <10). A structured knowledge questionnaire on prehypertension and hypertension will be used to assess knowledge on the subject. The questionnaire consists of 30 items, with a maximum score of 30. The items are based on the Joint National Committee 7 recommendations for nonpharmacological interventions in the management of prehypertension. Knowledge levels will be classified as poor (a score of 0-9), average (a score of 10-20), or good (a score of 21-30). Blood pressure will be assessed using a digital blood pressure apparatus. The baseline blood pressure will be measured after a 5-minute to 10-minute rest period. Two readings will be taken 1-3 minutes apart, and the average will be calculated. In case of a difference of more than 5 mmHg between the 2 readings, an additional 2 readings will be obtained, and the average of these multiple readings will be used [32]. Prehypertension will be identified among young adults based on the average of 2 blood pressure readings. The same procedure will be followed during the follow-up sessions at 1, 3, and 6 months. A calibrated stadiometer and weighing machine will be used to assess the heights and weights of the participants.

The validated tools were tested for reliability on 20 students from the selected degree colleges in Udupi District. The reliability of the structured knowledge questionnaire was assessed using the split-half method (*r*=0.911). The tools were pretested with 10 students from a degree college in Udupi District. A pilot study was conducted with 20 students at a selected degree college.

### Ethical Considerations

The study protocol received institutional ethical approval on May 11, 2022 (IEC1 160/2022) and is registered under the Clinical Trial Registry of India (CTRI/2023/04/051784). All the participants will receive a subject information sheet in both Kannada and English to help them understand the study. Written informed consent will be obtained from all participants prior to data collection. The study will adhere to the guidelines of the Declaration of Helsinki. The confidentiality and anonymity of the participants will be maintained.

### Statistical Analysis

Data analysis will be conducted using jamovi (version 2.3.21; The jamovi project), using both descriptive and inferential statistics in line with the study objectives. For descriptive statistics, means and SDs will be used because all study outcomes are quantitative and continuous. Because the study involves assessing outcomes at 4 time points (baseline, 1 month, 3 months, and 6 months), repeated measures ANOVA will be used to evaluate the effectiveness of the intervention, and per protocol analysis will be used.

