## Methods

### Study Design

#### Overview

The study is designed to be carried out in 2 phases. A cross-sectional survey design was used in phase 1. Because the study aims to evaluate the effect of the mHealth program on adherence to lifestyle practices, knowledge of prehypertension, and blood pressure, a pragmatic randomized controlled trial with cluster randomization was implemented in phase 2. The protocol follows the SPIRIT (Standard Protocol Items: Recommendations for Interventional Trials) 2013 checklist [24], which is provided in Multimedia Appendix 1. The CONSORT (Consolidated Standards of Reporting Trials of Nonpharmacologic Interventions) 2017 flowchart of the study is presented in Figure 2 [25-28].

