**Figure 2 figure2:**
[figure not shown]
CONSORT (Consolidated Standards of Reporting Trials of Nonpharmacologic Interventions) 2017 flow diagram for the study. N denotes the number of colleges (ie, clusters) and n denotes the number of participants per cluster. DASH: dietary approach to stop hypertension.

#### Phase 1

After obtaining administrative permission from the Institutional Research Committee, Institutional Ethical Committee, and Joint Director of Collegiate Education, Udupi District, taluks from Udupi District were randomly selected to collect data for assessing the prevalence of prehypertension in phase 1. The data were collected on-site from young adults of colleges from randomly selected taluks. Baseline information, clinical variables, lifestyle practices, knowledge on prehypertension and hypertension, and blood pressure were measured for all participants from the selected colleges. An automated, digital, oscillometric blood pressure machine (Omron) was used to measure blood pressure after device calibration. As of March 29, 2024, phase 1 was completed with data collected from 762 samples from 8 randomly selected colleges.

#### Phase 2

Colleges with students having prehypertension identified during phase 1 were considered as clusters (N=6) and will be allocated to the intervention (N=3) and control groups (N=3) by simple randomization using the chit method. A random allocation sequence using the chit method was generated by research assistants who are not involved in the study. Currently, phase 2 is in progress.

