**Phase 2**
Inclusion criteriaYoung adults identified to have prehypertension in phase 1.Young adults with prehypertension willing to participate in the study.Young adults with prehypertension having android mobile phones.Colleges with students having prehypertension identified during phase 1 were considered.Exclusion criteriaYoung adults identified to have hypertension in phase 1 and who were already diagnosed with other systemic disorders.Young adults with prehypertension who are on medications for any other ailments.Young adults with prehypertension who do not have android mobile phones.

The calculated sample size for phase 1 was determined to be 381 participants using the following formula for estimating a proportion, where n is the sample size required, Z_1-α/2_ is the desired confidence level (ie, for a 95% confidence level, Z_1-α/2_=1.96), P is the prevalence, and d is the margin of error:

This calculation assumes the prevalence of prehypertension among young adults to be 45% at a 95% confidence level with a 5% margin of error (absolute precision) based on a previous study by Kini et al [7]. After multiplying by a design effect of 2 due to cluster sampling, the sample size was determined to be 762 participants.

The sample size for phase 2 was 34 participants per group, considering a 38% anticipated population SD of the primary outcome variable (ie, the prevalence of prehypertension) obtained using the equation for repeated measures ANOVA given below. In the equation, n is the sample size required, Z_1-α/2_ is the desired confidence level (ie, for a 95% confidence level, Z_1-α/2_=1.96), Z_1-β_ is the power of the test (ie, for a power of 80%, Z_1-β_=0.84), σ² is the population variance (ie, square of the SD), m is the number of groups being compared, ρ is the correlation coefficient between groups, and d is the minimum detectable difference.

Accounting for a 20% dropout rate, the final sample size was 43 participants per group. After multiplying by a design effect of 2 due to cluster randomization, the sample size was determined to be 85 participants per group.

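### Six colleges are randomised, but the only stated effectiveness test is a repeated measures ANOVA with no college term, so false positives are inflated

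*Protocol article*

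**What the plan says.** The Overview under Study Design states that "a pragmatic randomized controlled trial with cluster randomization was implemented in phase 2". Under Phase 2, the colleges "were considered as clusters (N=6) and will be allocated to the intervention (N=3) and control groups (N=3) by simple randomization using the chit method". The sample size text in Study Participants and Sampling starts from 34 per group, allows for 20% dropout, and ends: "After multiplying by a design effect of 2 due to cluster randomization, the sample size was determined to be 85 participants per group".

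The Statistical Analysis section gives one inferential method for effectiveness: "repeated measures ANOVA will be used to evaluate the effectiveness of the intervention, and per protocol analysis will be used". The reason given is that outcomes are measured at four time points. College does not appear in the analysis as a random effect, a nested factor, a basis for robust variance or a unit of summary.

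**The concern.** The unit of randomisation is the college, so the arm comparison must be judged against variation between colleges. A standard repeated measures ANOVA judges it against variation between students. With 170 students, the between-subject test of arm would use 170 − 2 = 168 residual degrees of freedom, or 136 − 2 = 134 if 20% drop out. Six colleges in two arms provide 6 − 2 = 4.

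The design effect in the sample size does not repair this. It preserves planned power only if the analysis also uses the larger variance. If the analysis ignores college, the doubled sample just shrinks a standard error that is already too small.

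Blood pressure (primary), adherence and knowledge (secondary) are all to be analysed this way. A chance difference between two sets of three colleges could be reported as an effect of the app, and the Discussion says that positive results would support extending the app to the wider population.

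**Working it through.** **Inputs from the Protocol article:** 6 colleges, 3 per arm; 34 per group before inflation; dropout 20%; design effect (DE) 2; 85 per group; Z = 1.96 (two-sided 5%) and 0.84 (80% power); 4 visits. The article states no intracluster correlation (ICC), so the ICC values below are either back-calculated or assumed.

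**1. The plan's own figure.** 34 / (1 − 0.20) = 42.5, rounded up to 43. 42.5 × 2 = 85. The chain reproduces. The starting 34 cannot be checked, because the minimum detectable difference and the correlation have no stated values.

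**2. ICC implied by DE = 2.** DE = 1 + (m − 1) × ICC, with m = 85/3 = 28.3 students per college, gives ICC = 1/27.3 = 0.037. With 68 completers per arm, m = 22.7 and ICC = 1/21.7 = 0.046.

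**3. Error of a test that ignores college** (normal approximation). The ratio of naive to true standard error is 1/√DE, and the true two-sided error is 2 × (1 − Φ(1.96/√DE)). At DE = 2 the ratio is 0.71 and the error is 2 × (1 − Φ(1.386)) = 16.6%. For a range of ICCs at m = 28.3:

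| ICC | DE | Naive SE / true SE | True error |
|---|---|---|---|
| 0.01 | 1.27 | 0.89 | 8.2% |
| 0.02 | 1.55 | 0.80 | 11.5% |
| 0.037 | 2.00 | 0.71 | 16.6% |
| 0.05 | 2.37 | 0.65 | 20.3% |
| 0.10 | 3.73 | 0.52 | 31% |

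**4. Simulation of the ANOVA itself.** No true effect, 6 colleges of 28, 4 visits, ICC 0.0366, assumed within-person correlation 0.6, 4,000 trials per scenario. The correlation of a college's effect between visits (autocorrelation) was varied:

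| College autocorrelation | ANOVA arm main effect | ANOVA arm-by-visit | t-test on college mean change |
|---|---|---|---|
| 1.0 (constant) | 20.8% | 5.4% | 4.8% |
| 0.8 | 18.6% | 15.2% | 5.4% |
| 0.5 | 16.1% | 30.8% | 4.1% |

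The main effect can exceed 16.6% because averaging four visits removes within-person noise but not a constant college effect. With constant college effects, the ICC of the student mean is 0.0366 / (0.6 + 0.4/4) = 0.052, so DE = 1 + 27 × 0.052 = 2.41 and the error is 2 × (1 − Φ(1.96/√2.41)) = 20.7%, which agrees with the simulated 20.8%.

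A second simulation, with within-person correlation 0.5, gave the same pattern. With constant college effects at ICC 0.0366, the main effect rejected 22% and the interaction 5%. Adding a college-by-visit variance share of 0.01 or 0.02 raised the interaction to 16% and 30%. The college-level t-test stayed between 4.5% and 5.1% in every clustered scenario.

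**5. Power of a valid test.** The critical t on 4 df is 2.78, against 1.97 on 168 df. Take the effect that 34 independent students per group detect with 80% power. With 68 completers per arm at DE = 2, the effective size is 68/2 = 34 and the standardised effect is 1.96 + 0.84 = 2.80. On 4 df this gives about 56% power. With all 85 per arm it is 2.80 × √(85/68) = 3.13, or about 65%.

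**The case against.** Three points can be made for the plan.

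- **The participant-level reading is an inference.** The section is two sentences in a journal article, and an unseen analysis plan might adjust for college. But the article does not leave the method open. It names one that by default treats participants as independent. If a fuller plan handles clustering, this sentence still needs correcting.
- **The natural test with a baseline visit is arm-by-visit, which cancels stable college differences.** This is right, and that test then holds about 5%. It requires college effects to be exactly constant over visits. Measurements are taken on-site, and Table 2 shows that the visit windows at baseline and 1 month differ between arms, so some college-specific change between visits is plausible. The size of that change is an assumption; no figure in the article fixes it. Nor does the article say which ANOVA term is the test of effectiveness.
- **A design effect of 2 looks like a round multiplier.** Phase 1 uses the same factor with 762/8 = 95 students per college, which implies an ICC of 1/94 = 0.011. Carried to 28.3 per college, this gives DE = 1.29 and an error of about 8.4%, half the 16.6%. Phase 1 estimates a prevalence, so this is no better an estimate for blood pressure, but it does show that the size is uncertain.

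The second and third points change the size of the inflation. They do not remove the conflict between design and analysis.

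**Conclusion.** The concern holds: the analysis is wrong as written. The article randomises colleges, sizes the trial for clustering, and then fixes a test that does not account for it. On the protocol's own design effect, a participant-level comparison has a true two-sided error of about 17% instead of 5%, and about 8% to 31% for ICCs of 0.01 to 0.10. For the arm-by-visit term, the error runs from 5% when college effects are constant over visits to about 31% at an autocorrelation of 0.5.

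These figures assume equal colleges of about 28, a back-calculated or assumed ICC, and within-person correlations of 0.5 to 0.6. The direction depends on none of these values: any positive ICC inflates the main effect, and any college-specific change over time inflates the interaction. Because the primary and both secondary outcomes are affected, this must be fixed before phase 2 is analysed.

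**What to change.** Replace the repeated measures ANOVA in Statistical Analysis with one prespecified method that carries the college, and name the contrast and visit that define effectiveness. Two options are valid:

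- **Two-stage analysis:** adjust each participant's outcome for baseline, average within college, and compare the three means per arm by a t-test on 4 df. This is the simpler choice, and it avoids estimating several variance components from six colleges.
- **Linear mixed model:** random effects for college, college-by-visit and participant, with Kenward-Roger or Satterthwaite degrees of freedom. If this is chosen, name the two-stage analysis as the fallback should the model fail to fit.

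Report the observed ICC for each outcome. Do not make a permutation test the sole test: 3 versus 3 allows only 20 allocations, so the smallest two-sided p value is 2/20 = 0.10.

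The cost is a revised analysis paragraph and a different routine in the software, with no new data. Table 2 expected six-month visits to finish by June 30, 2025, so the change should be dated and recorded before the outcome data are analysed. Confidence intervals will be wider, and the restated power on 4 df is about 56% to 65% under the assumptions above. That shortfall comes from having three colleges per arm and is not created by the corrected analysis.

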**Figure 3 figure3:**
[figure not shown]
User flow diagram for the mHealth app on prehypertension. HTN: hypertension.

A screenshot of the mHealth app is presented in Multimedia Appendix 2. To evaluate the validity and applicability of eHealth trials, the CONSORT-EHEALTH (Consolidated Standards of Reporting Trials of Electronic and Mobile Health Applications and Online Telehealth) checklist [29] was used and is provided in Multimedia Appendix 3. To check the quality and usefulness of the mHealth app, the mobile application rating scale (Multimedia Appendix 4) [30,31] was used by 12 participants from the experimental group after a few days of app usage. The participants’ responses are provided in Multimedia Appendix 5. Due permission was obtained from the original author for using the mobile application rating scale.

Both the control and intervention groups will receive education on prehypertension. The experimental group will also receive the mHealth app free of cost, provides information on prehypertension, risk factors for prehypertension, lifestyle modifications (including the DASH diet and exercise), and strategies for preventing hypertension and its complications. The mHealth app (INFOBP) will be installed on the mobile devices of all students in the intervention group, and they will receive orientation on its use. The experimental group will be monitored for adherence to lifestyle practices every 15 days through the mobile app, and reinforcement and reminder messages will be sent to nonresponders. All participants in the experimental group will receive a message of encouragement through the app every 15 days to continue practicing the recommended lifestyle changes. The participants will also be able to view the comparative report of their clinical parameters (BMI and blood pressure) and the result of the data entered by them (knowledge and lifestyle adherence scores) during every assessment as feedback. Both groups will be followed up after 1, 3, and 6 months to assess their knowledge on prehypertension and adherence to lifestyle practices and record their height, weight, BMI, and blood pressure on-site. At the end of the study, an information booklet on prehypertension will be provided to every college in Udupi District that was included in the study.

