### Outcomes

The primary outcome is blood pressure, and the secondary outcomes are adherence to lifestyle practices and knowledge on prehypertension and hypertension.

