Smartphones are becoming a part of almost everyone’s lives, serving as essential tools for work, leisure, and communication. Smartphones are changing the way health education is delivered, promoting wellness activities and easing the management of diseases across a wide spectrum of populations [34]. The anticipated success of the mHealth app used in this study can be attributed to its customized approach. The app was developed as a blended approach to assess knowledge and lifestyle practices, track clinical parameters of participants with prehypertension, and disseminate information pertaining to health promotion. Any positive outcomes observed in this study would suggest that the mHealth app can be successfully used, supporting its extension to the population at large.

This protocol addresses a burning issue, and the methodology emphasizes assessing the real-world impact of the mHealth app. The effectiveness of digital health interventions in managing hypertension has led to successful blood pressure control. This approach could also be explored for its potential in weight management and obesity prevention. By supporting healthy weight maintenance and encouraging the development of healthy eating habits, particularly among students, these interventions may contribute to improved heart health and, more significantly, help prevent hypertension and CVDs [35-37]. Another study found that a youth-led digital intervention was effective in controlling blood pressure among adults with hypertension [38]. The growing population in India, coupled with increasing risk factors, supports the importance of primary prevention as a critical strategy to combat this epidemic. Based on the relevant research and existing data, this protocol underlines the importance of mobile health interventions in addressing prehypertension among young adults in this digital era.

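### Per protocol, undefined, is the only analysis set named for a pragmatic trial; it gives up the comparison as randomised and probably favours the app

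*Protocol article*

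**What the plan says.** The Study Design overview in Methods states that "a pragmatic randomized controlled trial with cluster randomization was implemented in phase 2", and the title and abstract use the same label. The Study Overview in the Discussion adds that "the methodology emphasizes assessing the real-world impact of the mHealth app".

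The Outcomes section states: "The primary outcome is blood pressure". Lifestyle adherence and knowledge are secondary outcomes. Under Phase 2 in Methods, six colleges "will be allocated to the intervention (N=3) and control groups (N=3) by simple randomization using the chit method".

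The Statistical Analysis section says that "repeated measures ANOVA will be used to evaluate the effectiveness of the intervention", over four time points (baseline, 1, 3 and 6 months), and in the same sentence that "per protocol analysis will be used". It does not say what makes a participant per protocol. No intention-to-treat, as-allocated or sensitivity set is mentioned anywhere in the article.

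The mHealth App section gives the education to both groups. The app goes only to the experimental arm: "The experimental group will be monitored for adherence to lifestyle practices every 15 days through the mobile app", with reminders to those who do not respond. Both groups are seen on site at 1, 3 and 6 months.

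**The concern.** The stated question is whether providing the app lowers blood pressure under ordinary conditions. Those conditions include students who install the app and stop using it. A per-protocol set in its ordinary meaning removes such students, so the estimate describes compliers rather than the effect of offering the app. Per protocol is also not the cautious choice in a trial that seeks to show a benefit.

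The exclusions are made after allocation and may depend on behaviour related to blood pressure. Students who disengage are plausibly less motivated and have less healthy habits. The experimental arm has requirements that controls cannot fail: using the app and answering its 15-day checks. A rule built on those requirements would leave a selected app arm to be compared with a less selected control arm.

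The missing definition adds a further risk. The Data Collection section classes a participant as adherent at a score of at least 10 out of 12, and that adherence is itself a secondary outcome. Nothing in the article prevents this cut-off from defining the per-protocol set, in which case the trial would condition on one of its own outcomes.

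**Working it through.** **The plan's own figures.** The sample size section starts from 34 per group. Allowing for 20% dropout gives 34 / (1 − 0.20) = 42.5, reported as 43. Multiplying by the design effect of 2 gives 42.5 × 2 = 85 per group, so the chain reproduces. The starting value of 34 cannot be checked, because the article gives no value for the detectable difference or the correlation. Nothing in this point depends on it. Analysing by allocated arm leaves 85 per group unchanged, because the dropout allowance is already included.

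**Size of the bias: simple model.** Assume no true effect. Let q1 and q0 be the fractions excluded from the app and control arms. Let D1 and D0 be how much higher the systolic pressure of those excluded is than that of those retained in the same arm. A whole-arm mean equals the retained mean + q × D, so exclusion lowers the analysed mean by q × D. The spurious benefit is therefore

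bias = q1 × D1 − q0 × D0.

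The article gives none of these inputs; all are assumed.

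| q1 | D1 (mmHg) | q0 | D0 (mmHg) | Spurious benefit (mmHg) |
|---|---|---|---|---|
| 0.20 | 2 | 0 | – | 0.4 |
| 0.30 | 3 | 0 | – | 0.9 |
| 0.40 | 4 | 0 | – | 1.6 |
| 0.20 | 3 | 0.20 | 3 | 0.6 − 0.6 = 0 |
| 0.10 | 3 | 0.20 | 3 | 0.3 − 0.6 = −0.3 |

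The first three rows set control exclusions to zero. The last two show that the bias disappears or changes sign when they are not zero.

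**Second model, as a check.** Suppose the least adherent fraction of each arm is excluded, and adherence has correlation r with the fall in blood pressure, whose SD is s. With c1 and c0 the standard normal quantiles of q1 and q0, and φ the standard normal density,

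bias = r × s × [φ(c1)/(1 − q1) − φ(c0)/(1 − q0)].

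Assume s = 8-10 mmHg and r = 0.1-0.5:

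- 20% of the app arm and no controls excluded: the bracket is 0.350, so the bias runs from 0.1 × 8 × 0.350 = 0.3 to 0.5 × 10 × 0.350 = 1.8 mmHg.
- 40% and 10%: the bracket is 0.644 − 0.195 = 0.449, so 0.4 to 2.2 mmHg.
- 20% and 20%: zero.
- 10% and 20%: the bracket is 0.195 − 0.350 = −0.155, so −0.1 to −0.8 mmHg.
- The bias is zero if r = 0 and changes sign if r is negative.

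Starting from 85 per arm before exclusions and ignoring clustering, the nominal 5% two-sided error becomes about 5.5%-19% in the first case and 5.7%-24% in the second. The two models agree on order of magnitude and on the conditions under which the bias vanishes or reverses.

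**Interaction with the model.** Repeated measures ANOVA in its classical form uses only participants with all four measurements. Deleting the words on per protocol would therefore not give an analysis of everyone as allocated, because anyone missing a single visit would still drop out.

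**The case against.** The article condenses a fuller plan, and an unseen SAP may define the per-protocol set or add other sets. That can excuse missing detail. It does not excuse the choice itself, which the article makes and publishes.

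Three stronger readings are tempting, and the article does not support them.

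- A reader might infer that exclusions fall only on the app arm, leaving an untouched control group. Controls also receive the teaching, attend the same visits and complete the same adherence scale, so a rule based on any of these would exclude from both arms. Reminders and encouragement go only to the app arm, which could even make control losses the larger.
- A reader might infer that the app's effect is certain to be inflated. That depends on a definition the article does not give, and the calculations include cases with zero and negative bias.
- A reader might infer that randomisation as a whole is discarded. The colleges stay in their allocated arms; what is lost is comparability of the participants within them. With three colleges per arm drawn by lot, balance is fragile to begin with.

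What remains is that an undefined post-allocation exclusion is the only named basis for the main result of a trial described as pragmatic.

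**Conclusion.** The point holds and should be fixed before analysis, because the analysis set governs the primary result. Per protocol does not match the stated effectiveness question, whichever way it errs. Bias in favour of the app is the likely direction, since only that arm has app-related requirements to fail, but it is not established. The illustrative 0.4-1.6 mmHg rests on assumed exclusion rates and pressure differences and on no control exclusions. It indicates scale and does not predict this trial's bias.

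**What to change.** Replace the per-protocol sentence and the model together:

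- **Primary analysis:** all enrolled phase 2 participants, in the arm to which their college was allocated, regardless of app use or adherence.
- **Model:** a mixed model for repeated measures with a college effect, in place of complete-case repeated measures ANOVA. It keeps participants with incomplete follow-up. State the assumption made about missing visits.
- **Per protocol:** supportive only, with a written definition that can be applied to both arms and does not use the lifestyle adherence score.
- **Timing:** record the change in a dated amendment before outcome data are examined. Table 2 expected the six-month visits to finish by June 30, 2025, and the article appeared on August 7, 2025, so the amendment should state what data had been seen by its date.

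The cost is a short amendment and a little more analysis work. The on-site visits are planned for both groups with no exemption for students who stop using the app, so no new data collection is implied. The article does not say whether students who withdraw are followed. The target of 85 per group stands. The estimated effect will probably be smaller, but it will answer the question the trial asks.
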